| 1. Project synopsis |  |
| --- | --- |
| **Name of the Funding Source:** TBC | **Protocol Number:** V.5 |
| **Study Title:** Effects of Tai Chi on the quality of life, mental wellbeing, and physical function of adults with chronic diseases: protocol for a single-blind, two-armed, randomised controlled trial | |
| **Short Title:** Tai Chi for chronic disease management: a trial protocol | |
| **Planned Study Sites:** ECU Sport Centre and or local communities, Perth, Australia | |
| **Number of Participants:** Forty adults aged 18 years and older, diagnosed with one or more chronic disease (e.g., pain, diabetes, cancer), will be included in this study. | |
| **Chief Investigator:**  [name]  School of Nursing and Midwifery  Edith Cowan University  Western Australia, 6027 | |
| **Study Period:** 03/01/2022—02/03/2032  Date of first participant enrolment: 01/06/2022 Estimated date of last participant completed: 02/12/2023 | |
| **Objectives:**  The overarching aim of this study is to provide compelling evidence on the therapeutic efficacy of the Tai Chi/Qigong—Body & Mind Medicine program chronic disease management | |
| **Study Design:** This is a single-blind (assessors blind to group allocation), double-armed, randomised controlled trial on the therapeutic effect of a 12-week Tai Chi/Qigong exercise for Australia adults | |
| **Study Criteria**  **Key inclusion criteria**  Adults who are aged between 18 years and older willing and able to consent  **Key exclusion criteria**  Inclusion criteria consist of (1) adults aged 18 years and older, (2) diagnosed with one or more chronic disease (e.g., pain, diabetes, cancer), (3) having no physical and mental limitations prohibiting exercise, and (4) willing and able to consent for participation in the trial. People who are pregnant or with a serious health conditions that incapable of completing 12-week Tai Chi exercise will be ineligible to participate. | |
| **Intervention and exposure:**  Intervention group:  Participants will receive a 12-week Tai Chi/Qigong exercise from a licensed acupuncturist at ECU Holistic Health Research Clinic within ECU Sport Centre. 45 minutes per session, three times a week for twelve weeks. Although the program runs three times per week, but participants are expected to attend any of two sessions within that week. At the beginning (baseline, T0) and the end of receiving twelve weeks Tai Chi/Qigong exercise (post trial, T1), participants will be asked to complete the baseline (T0) and the post-trial (T1) online questionnaires. The researchers will also conduct a set of objective assessments in the clinic at T0 and T1.  Control group:  Waiting list control with usual care (e.g., other exercise) over the 12-week trial period.  Participants in this group will be informed via email that they are in the waiting list group but will be asked to complete the baseline (T0) and the post-trial (T1) online questionnaires. The researchers will also conduct a set of objective assessments in the clinic at T0 and T1. Participates in this group will join the next batch training in 12 weeks’ time as the Tai Chi/Qigong—Body & Mind Medicine program is an ongoing activity. | |
| **Outcome measures and time points:**  The outcomes are QoL as measured by mean scores on the 12-item Short Form Health Survey (SF-12) and the EuroQoL (EQ-5D); anxiety as measured by mean scores on generalized anxiety disorder 7 (GAD-7); depression as measured by mean scores on the patient health questionnaire (PHQ-9); work productivity and activity assessment (WPAI:SHP) questionnaire; pain as measured by mean scores on the visual analogue scale (VAS), and the McGill pain questionnaire (MPQ). These outcomes will be measured via two online surveys prior to (T0) and post-intervention (T1). Questions on participants’ non-pharmacologic therapy preferences and experiences of participating in the trial will also be included, and measured at T0 and T1, respectively.  In addition to these self-reported questionnaires conducted via online surveys, objective measures will also be carried out by the research team at ECU Holistic Health Research Clinic, which is in the university’s Sport Centre where the Tai Chi/Qigong training program take place. These measures include flexibility as measured by the finger to floor distance (FFD); obesity as measured by mean scores on body mass index (BMI); Vital signs (blood pressure, heart rate, respiratory rate, temperate, and oxygen saturation) as measured by a blood pressure monitor, tympanic, and pulse oximetry device. These outcomes will be measured prior to (T0) and post-intervention (T1). People diagnosed with pre-diabetes or diabetes, their HbA1C and fasting BGL will also be measured via test kits at T0 and T1. | |
| **Sample Size:** Based on previous Tai Chi/Qigong exercise intervention studies, n = 20 participants will be required per group (total n=40) for this study. | |

Element 1

**Aims or Questions**

Project title: Impact of Tai Chi/Qigong—Body & Mind Medicine program on Australian adults’ health

The overarching aim of this study is to provide compelling evidence of the therapeutic efficacy of the Tai Chi/Qigong—Body & Mind Medicine program for chronic disease management.

**Benefit of exploring these research questions**

Several studies demonstrated that Tai Chi/Qigong has many health benefits, such as decreased heart rate, decreased blood pressure, lowered lipid levels, decreased levels of stress hormones, enhanced immune function, and improved physical wellbeing and psychological wellbeing. However, there is no consolidated conclusion for Tai Chi/Qigong and more studies in this field are required to provide updated evidence. Therefore, this study aims to address this knowledge gap.

We hypothesize that Quality of life (QoL) in Tai Chi/Qigong group is better than the control group (usual care). We hope that the results of our research can be used to inform our knowledge about how to better manage chronic diseases that many Australians are suffering.

There are no foreseeable risks associated with this research project.

**Outline the design of this research; its methods and details of the instruments to be used to collect the data, including psychometric properties if applicable.**

**Study design:**

This is a single-blind (assessors blind to group allocation), double-armed, randomised controlled trial on the therapeutic effect of a 12-week Tai Chi/Qigong exercise for Australia adults

**Study type:**

Interventional study

**PICOs:**

**P:** Adults aged 18 years and older will be recruited for this trial

**I:** 12-week Tai Chi/Qigong exercise + usual care

**C:** Waiting list control with usual care (e.g., other exercise)

**O:**

The primary outcome is quality of life as measured by mean scores on the 12-item Short Form Health Survey (SF-12) and the EuroQoL (EQ-5D). This outcome will be obtained via two online surveys: at baseline (T0) and post intervention (T1).

The secondary outcomes will include anxiety as measured by mean scores on generalized anxiety disorder 7 (GAD-7); depression as measured by mean scores on the patient health questionnaire (PHQ-9); work productivity and activity assessment (WPAI:SHP); pain as measured by mean scores on the visual analogue scale (VAS) and the McGill pain questionnaire (MPQ). These outcomes will be measured via two online surveys at T0 and T1. Questions on participants’ non-pharmacologic therapy preferences and experiences of participating in the trial will also be included, and measured at T0 and T1, respectively. Flexibility as measured by the finger to floor distance (FFD); obesity as measured by mean scores on body mass index (BMI); blood pressure (BP), and oxygen saturation (SpO2) as measured by a pulse oximetry device will also be carried out by the researchers, and these outcomes will be measured before the intervention (T0) and post intervention (T1).

**S:** This is a single-blind (assessors blind to group allocation), double-armed, randomised controlled trial on the therapeutic effect of a 12-week Tai Chi/Qigong exercise for adults.

**Key inclusion exclusion criteria**

Inclusion criteria consist of (1) adults aged 18 years and older, (2) diagnosed with one or more chronic disease (e.g., pain, diabetes, cancer), (3) having no physical and mental limitations prohibiting exercise, and (4) willing and able to consent for participation in the trial. People who are pregnant or with a serious health conditions that incapable of completing 12-week Tai Chi exercise will be ineligible to participate.

**Intervention and exposure:**

**Intervention group:**

In addition to usual care, participants will receive a 12-week Tai Chi/Qigong exercise from a licensed acupuncturist at ECU Holistic Health Research Clinic within the sport centre. 45 minutes per session, three times a week for twelve weeks. Although the program runs three times per week, but participants are expected to attend any of two sessions within that week. At the end of twelve weeks receiving the Tai Chi/Qigong exercise, participants will receive an online link to complete the post-intervention questionnaires. The researchers will also complete the physical assessments in the clinic.

**Control group:**

Waiting list non-intervention but usual care (e.g., other exercise) over the 12-week trial period.

Participants in this group will be informed via email that they are in the no intervention waiting list group but will be emailed an online link to complete the post-intervention questionnaire and invited to the clinic to complete other physical assessments.

Participates in the non-intervention waiting list group will join the next batch as the Tai Chi/Qigong—Body & Mind Medicine program is an ongoing activity.

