Descriptive statistics for continuous variables will initially be described by mean and standard deviation (SD) for normal data, and by median and interquartile range (IQR) for non-normal data. Categorical data will be summarised by frequencies and proportions. The primary and secondary outcomes will be assessed following intention-to-treat principles. Linear mixed modelling with unstructured covariance matrix will be conducted to assess changes in outcomes throughout the study. This model allows for the inclusion of missing data in an intention-to-treat analysis without imputations (e.g., last-observation-carried-forward). Post-hoc tests will be conducted on all pairwise comparisons. The analysis will be adjusted for potential confounding factors such as age, gender, education levels and any other potentially relevant variables where data are available. The corrected Akaike Information Criterion (AICc) will be used to assess model fit when covariates are added to the model. Normality assumptions will be assessed using the Shapiro-Wilk test. If required, non-linear transformations such as the square root and log-transformations, will be applied to normalise the data. Statistical significance will be set at an alpha level of 0.05. False discovery rate (FDR). Corrections will be applied to all analysed outcomes to account for multiple comparisons. Effects sizes, defined by partial eta squared, will be reported and interpreted, with 0.01, 0.06 and 0.014, respectively, identified as small, medium and large effects (43). All analyses will be conducted using R version 4.1.

The qualitative data collected via open-ended questions across the two online surveys will be used to help explain or elaborate on the quantitative data. Qualitative data will be analysed using template thematic analysis. Template thematic analysis uses ‘a priori’ code frames to analyse and report on the data. The initial skeleton code frame is often formulated from the questions asked of participants and then built upon during analysis in an iterative process.

Element 2

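### Tai Chi is delivered in batches and the waiting-list control is not, but neither the mixed model nor the block randomisation accounts for batch; positive within-batch correlation would make the standard error too small

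*Protocol*

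**What the plan says.** **Delivery.** Under Intervention group, "participants will receive a 12-week Tai Chi/Qigong exercise from a licensed acupuncturist at ECU Holistic Health Research Clinic within the sport centre". The programme runs three 45-minute sessions a week, of which each participant is expected to attend two of their choice.

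**Batches.** Under Control group, waiting-list participants "will join the next batch as the Tai Chi/Qigong—Body & Mind Medicine program is an ongoing activity". The synopsis says the same: they "will join the next batch training in 12 weeks". Until then they receive usual care and no trial sessions. The number and size of batches are not given.

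**Randomisation.** Under Recruitment, individuals are allocated in randomised blocks after their baseline measurements. The stated purpose is to keep the arm sizes similar. No link to intake batch is mentioned.

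**Analysis.** Under Statistical analysis, "Linear mixed modelling with unstructured covariance matrix will be conducted to assess changes in outcomes throughout the study". The results are to be "adjusted for potential confounding factors such as age, gender, education levels and any other potentially relevant variables where data are available", with AICc used to judge added covariates and a false discovery rate correction for multiplicity. "Statistical significance will be set at an alpha level of 0.05". Batch and class are not mentioned.

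**Sample size.** The synopsis states that "n = 20 participants will be required per group (total n=40) for this study".

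**The concern.** People who train together over the same 12 weeks can come to resemble one another in outcome, through shared sessions, group dynamics and the way that run of the programme happened to go. Waiting-list controls have no such shared exposure. With one grouped arm and one ungrouped arm, the Tai Chi mean carries a between-batch variance component that the control mean lacks.

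With only two time points, the unstructured covariance most naturally describes the correlation between a person's own T0 and T1 values. It does not link different people in one batch. Run as described, the model would leave that component out of the standard error. Confidence intervals would be too narrow, and too many null effects would be declared significant, in a trial whose stated aim is compelling evidence of efficacy.

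Part of the remedy cannot wait for the analysis stage. Whether both arms are represented in every intake, and whether batch is recorded at all, is settled at enrolment.

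**Working it through.** **The plan's own figure.** The 20 per group cannot be reproduced. The synopsis gives its basis only as "Based on previous Tai Chi/Qigong exercise intervention studies", with no effect size, SD, power or dropout. For orientation, with two-sided 0.05 and 80% power, n per arm = 2(1.96 + 0.84)²/d² = 15.7/d², so 20 per arm corresponds to d of about 0.886 (15.7/0.785 = 20). No allowance for clustering is stated.

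**Inputs from the protocol.** 20 per arm; alpha 0.05 (sidedness not stated, two-sided assumed); grouping in the Tai Chi arm only.

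**Inputs assumed.**
- ICC within a Tai Chi batch of 0.02, 0.05 or 0.10, for the outcome as analysed.
- Number of batches k = 2, 4 or 6, so mean batch size m = 20/k = 10, 5 or 3.33.
- The upper limit of six comes from the synopsis dates. From 01/06/2022 to 02/12/2023 is 549 days, or 78.4 weeks, and 78.4/12 = 6.5, so six sequential 12-week batches fit. Overlapping batches, or the later data-collection end date given elsewhere in the protocol, would allow more.
- A two-sample t-test (38 df) stands in for the model's arm contrast.

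**Formulas.**
- Design effect in the Tai Chi arm: DE = 1 + (m − 1) × ICC.
- True over naive standard error of the difference: r = √((DE + 1)/2) = √((2 + (m − 1) × ICC)/2).
- Approximate type I error: 2 × (1 − Φ(1.96/r)).

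**Example.** For m = 10 and ICC 0.05: DE = 1 + 9 × 0.05 = 1.45; r = √(2.45/2) = 1.107; 1.96/1.107 = 1.771; type I error about 7.7%.

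| ICC | Batches | m | DE | r | Type I, formula | Type I, simulated |
|---|---|---|---|---|---|---|
| 0.02 | 2 | 10 | 1.18 | 1.044 | 6.0% | 6.1% |
| 0.02 | 4 | 5 | 1.08 | 1.020 | 5.5% | 5.4% |
| 0.02 | 6 | 3.33 | 1.047 | 1.012 | 5.3% | 5.3% |
| 0.05 | 2 | 10 | 1.45 | 1.107 | 7.7% | 7.5% |
| 0.05 | 4 | 5 | 1.20 | 1.049 | 6.2% | 6.1% |
| 0.05 | 6 | 3.33 | 1.117 | 1.029 | 5.7% | 5.7% |
| 0.10 | 2 | 10 | 1.90 | 1.204 | 10.4% | 10.5% |
| 0.10 | 4 | 5 | 1.40 | 1.095 | 7.4% | 7.4% |
| 0.10 | 6 | 3.33 | 1.233 | 1.057 | 6.4% | 6.4% |

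The simulations used at least 100,000 trials per setting, and repeat runs differ by 0.1 to 0.2 percentage points. At ICC 0 the simulated error is 5.0% for any number of batches.

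**Edge cases.**
- *One batch of 20.* The naive error would be 10.9% at ICC 0.05, but the batch effect is then fully confounded with arm and no model can estimate it.
- *Batch effect shared equally by both arms* (an intake-period effect). The naive test is slightly conservative: 4.2% to 4.6% for ICC 0.05 to 0.10 with two or four batches.
- *Batch added as a fixed main effect.* With clustering in the Tai Chi arm only, the error at ICC 0.05 is still about 7.8% with two batches and 6.4% with four. The clustering acts as a batch-by-arm effect, which a batch main effect does not absorb.

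**The case against.** The strongest objection is that this is silence rather than error. The protocol does not say that participants are treated as independent, its covariate list is open-ended, and a batch random effect could be set in a statistical analysis plan that is not shown. That stands against any claim that the protocol assumes independence. It does not dispose of the point. The protocol fixes the model, covariance, covariates, fit criterion and multiplicity method without batch. Its open-ended clause concerns confounders, not a variance component. Tying randomisation to intake and recording batch are also design steps that a later analysis plan cannot supply.

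A reader might infer four stronger things that the documents do not support:

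- **That the type I error does exceed 5%.** This depends on an ICC and a number of batches that the protocol does not give. At ICC 0.02 with six batches the excess is about 0.3 percentage points, and at ICC 0 there is none.
- **That a single instructor adds clustering the model should correct.** The number of instructors is not stated. If there is only one, that effect is common to all treated participants and confounded with arm. It limits generalisability, and no batch term removes it.
- **That season separates the arms.** Controls randomised at the same time live through the same calendar period. Variation of that kind is plausibly shared, and ignoring it makes the test slightly conservative.
- **That participants sit in fixed classes.** Choosing any two of three weekly sessions mixes attendance within an intake, so the cluster is the batch and not the class.

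The sentence about joining a later batch concerns controls after their wait. It shows that the programme runs in batches, but not how the 20 Tai Chi participants are divided. Group delivery is itself inferred from the scheduled sessions and batch training.

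**Conclusion.** The point holds conditionally and should be addressed. The design is partially nested, and neither the described model nor the randomisation deals with batch. If the within-batch correlation is positive and confined to the Tai Chi arm, the naive standard error is too small. For an ICC of 0.02 to 0.10 and two to six batches, the true value is about 1.01 to 1.20 times the naive one. Equivalently, the naive value is about 1% to 17% too small (1 − 1/1.20 = 0.17). The two-sided type I error is then about 5.3% to 10.5%. The upper end needs both few batches and a high ICC. The ICC, the number of batches and equal batch sizes are assumptions, so the size of the problem is a range and not a finding about this trial's actual error rate.

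**What to change.** 1. Under Recruitment, state the planned number of batches, randomise in blocks within each intake so that both arms occur in every batch, and record the batch for each participant.
2. Under Statistical analysis, add a sensitivity analysis of the primary outcome with a random batch effect in the Tai Chi arm only and small-sample degrees of freedom.
3. If there are too few batches to estimate that effect, report the primary confidence interval with its half-width multiplied by √((2 + (m − 1) × ICC)/2) for ICC 0.02 to 0.10, where m is the batch size.
4. Optionally, add batch as a fixed effect to remove intake-period variation common to both arms, and state that this does not correct clustering in the Tai Chi arm.
5. Report the instructor effect as a limit on generalisability.

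The cost is one recorded variable, a little more analysis and a slightly wider interval in the sensitivity analysis: between about 1% and 20% wider over the range above. The optional fixed effect also uses a few degrees of freedom.

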**How the planned methods achieve the aim or research questions**

The primary outcome is quality of life as measured by mean scores on the 12-item Short Form Health Survey (SF-12) and the Quality-of-life scale (QOLS). This outcome will be obtained via two online surveys: at baseline (T0) and post intervention (T1).

The secondary outcomes will include anxiety as measured by mean scores on generalized anxiety disorder 7 (GAD-7); depression as measured by mean scores on the patient health questionnaire (PHQ-9); work productivity and activity assessment (WPAI:SHP); pain as measured by mean scores on the visual analogue scale (VAS) and the McGill pain questionnaire (MPQ). These outcomes will be measured via two online surveys at T0 and T1. Questions on participants’ non-pharmacologic therapy preferences and experiences of participating in the trial will also be included, and measured at T0 and T1, respectively. Flexibility as measured by the finger to floor distance (FFD); obesity as measured by mean scores on body mass index (BMI); blood pressure (BP), and oxygen saturation (SpO2) as measured by a pulse oximetry device will also be carried out by the researchers, and these outcomes will be measured before the intervention (T0) and post intervention (T1).

Statistical analysis:

Descriptive statistics for continuous variables will initially be described by mean and standard deviation (SD) for normal data, and by median and interquartile range (IQR) for non-normal data. Categorical data will be summarised by frequencies and proportions. The primary and secondary outcomes will be assessed following intention-to-treat principles. Linear mixed modelling with unstructured covariance matrix will be conducted to assess changes in outcomes throughout the study. This model allows for the inclusion of missing data in an intention-to-treat analysis without imputations (e.g., last-observation-carried-forward). Post-hoc tests will be conducted on all pairwise comparisons. The analysis will be adjusted for potential confounding factors such as age, gender, education levels and any other potentially relevant variables where data are available. The corrected Akaike Information Criterion (AICc) will be used to assess model fit when covariates are added to the model. Normality assumptions will be assessed using the Shapiro-Wilk test. If required, non-linear transformations such as the square root and log-transformations, will be applied to normalise the data. Statistical significance will be set at an alpha level of 0.05. False discovery rate (FDR). Corrections will be applied to all analysed outcomes to account for multiple comparisons. Effects sizes, defined by partial eta squared, will be reported and interpreted, with 0.01, 0.06 and 0.014, respectively, identified as small, medium and large effects (43). All analyses will be conducted using R version 4.1.

The qualitative data collected via open-ended questions across the two online surveys will be used to help explain or elaborate on the quantitative data. Qualitative data will be analysed using template thematic analysis. Template thematic analysis uses ‘a priori’ code frames to analyse and report on the data. The initial skeleton code frame is often formulated from the questions asked of participants and then built upon during analysis in an iterative process.

Element 2

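### The plan orders tests on every pairwise comparison without marking the between-arm contrast that answers its hypothesis as the primary test

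*Protocol*

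**What the plan says.** The hypothesis, in the protocol section on the benefit of exploring the research questions, is between arms: "We hypothesize that Quality of life (QoL) in Tai Chi/Qigong group is better than the control group (usual care").

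The statistical analysis text, under the heading on how the planned methods achieve the aim, sets out the tests:

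- Model: "Linear mixed modelling with unstructured covariance matrix will be conducted to assess changes in outcomes throughout the study".
- Contrasts: "Post-hoc tests will be conducted on all pairwise comparisons".
- Covariates: "The analysis will be adjusted for potential confounding factors such as age, gender, education levels and any other potentially relevant variables where data are available".
- Covariate choice: "The corrected Akaike Information Criterion (AICc) will be used to assess model fit when covariates are added to the model".
- Significance level: "Statistical significance will be set at an alpha level of 0.05".
- Multiplicity: a false discovery rate method is named, and "Corrections will be applied to all analysed outcomes to account for multiple comparisons".

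There are two arms and two time points, T0 and T1. The synopsis gives the size: "n = 20 participants will be required per group (total n=40) for this study". The recruitment section places randomisation after the baseline survey and physical assessments. The text does not state the fixed effects, a group-by-time term, how the T0 value enters the model, or which comparison is primary.

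**The concern.** The hypothesis is about a difference between arms, but the tests are described as an assessment of change followed by all pairwise tests. No sentence connects the two. A reader who follows the text obtains six p-values per outcome with no order of importance, and two of them are before-after tests within one arm.

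Within-arm tests are a well-known source of false treatment claims. If Tai Chi reaches significance and control does not, that is easily read as a treatment effect, although the two arms have not been compared. The risk is credible here because the control arm's usual care may include other exercise, so both arms could improve.

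A second question is precision. With 40 participants it matters whether the reported between-arm estimate uses the T0 value of the outcome efficiently. Age, gender and education are named as covariates; the outcome's own T0 value is not.

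**Working it through.** **Inputs from the protocol.** Two arms, two time points, 20 per arm, alpha 0.05.

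**Inputs assumed, because the protocol gives none.** Two-sided tests, T0-T1 correlation r, a common improvement in both arms, equal SDs and complete data.

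**The plan's own figure.** The 20 per arm cannot be reproduced: no effect size, SD, power or dropout accompanies it. Working backwards for a two-sided test with 80% power on T1 means, the detectable standardised difference is (1.960 + 0.842) × √(2/20) = 0.89.

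**Step 1: count the comparisons.** Two arms × two times = 4 cells, and 4 × 3 / 2 = 6 pairs:

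| Pair | Number | Addresses the hypothesis? |
| --- | --- | --- |
| Tai Chi vs control at T1 | 1 | Yes |
| Tai Chi vs control at T0 | 1 | No (before treatment) |
| T1 vs T0 within one arm | 2 | No |
| One arm at T0 vs the other at T1 | 2 | No |

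**Step 2: error from within-arm reading.** 40,000 trials were simulated with 20 per arm, no treatment effect, the same improvement in both arms and unadjusted t-tests.

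| r | Common improvement (SD) | Tai Chi improves significantly | Tai Chi significant, control not | Between-arm test of change |
| --- | --- | --- | --- | --- |
| 0.5 | 0.3 | 24.7% | 18.5% | 5.1% |
| 0.5 | 0.5 | 56.4% | 24.4% | 4.8% |
| 0.7 | 0.3 | 37.6% | 23.7% | 5.0% |
| 0.7 | 0.5 | 78.4% | 17.1% | 5.1% |

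A separate run of 20,000 trials at r = 0.5 and improvement 0.45 SD gave 24.9% for the fourth column. The range is therefore about 17-25%.

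As a check, the arms are independent, so that column should be about p(1−p), where p is the third column: 0.564 × 0.436 = 0.246, against 0.244 simulated. The maximum of p(1−p) is 25%, at p = 0.5. With no change in either arm the figure falls to 2.3-2.5%, although at least one of the six unadjusted tests is then significant in 18-20% of trials.

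**Step 3: precision under three readings of the between-arm effect.** In units of 2σ²/n the variances are:

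- T1 contrast without baseline: 1
- Difference in change (group-by-time term, free baseline means): 2(1−r)
- T1 contrast adjusted for T0: 1−r²

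Relative to the adjusted contrast, the difference in change has variance 2(1−r)/(1−r²) = 2/(1+r), and the unadjusted T1 contrast has 1/(1−r²):

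| r | Difference in change | T1 without baseline |
| --- | --- | --- |
| 0.3 | 1.54 | 1.10 |
| 0.5 | 1.33 | 1.33 |
| 0.7 | 1.18 | 1.96 |
| 0.8 | 1.11 | 2.78 |

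These are large-sample ratios and ignore the small cost of estimating the slope.

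**Step 4: does the stated type of model have to lose precision?** No. Generalised least squares for T0 and T1 with unstructured covariance, in SD units with 20 per arm, gives these standard errors:

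| r | Common baseline mean | ANCOVA, √((1−r²) × 2/20) | Interaction, free baseline means |
| --- | --- | --- | --- |
| 0.5 | 0.274 | 0.274 | 0.316 |
| 0.7 | 0.226 | 0.226 | 0.245 |

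**Step 5: what this means for power.** At an assumed standardised difference of 0.8 and r = 0.3 / 0.5 / 0.7, power is 76% / 83% / 94% for the adjusted contrast, 57% / 72% / 90% for the difference in change, and 72% throughout for T1 without baseline.

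**The case against.** The strongest reply is that the pairwise tests are labelled post-hoc. They follow the mixed model and do not replace it, and they include Tai Chi versus control at T1. The text nowhere says that the between-arm effect will go untested. This stands. A reader might infer that the plan tests changes instead of comparing the arms; the documents do not support that. A difference in change is itself a valid between-arm test and holds its 5% level in Step 2.

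A reader might also infer that the plan wastes precision. That is not established either. The fixed effects are not given, a common baseline mean would match ANCOVA, and the covariate list is open and could admit the T0 value. If T0 is already a response in the model, it would not also be entered as a covariate.

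The exact model and contrast are commonly left to a statistical analysis plan, which may exist and is not shown. That disposes of any complaint about missing detail alone. It does not dispose of the pairwise sentence, which is a positive instruction: an analysis plan could add a primary contrast, but the protocol would still order the other five tests.

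The false discovery rate correction does not fully answer the point. It is stated for outcomes and is not clearly extended to contrasts within an outcome. Even if it were, correcting a within-arm p-value does not turn it into a comparison of arms.

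Finally, the harm requires someone to read within-arm p-values as a treatment effect, and nothing in the protocol says that the authors will.

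**Conclusion.** The point holds in a limited form. The protocol orders all pairwise tests and does not mark the one contrast that answers its hypothesis as primary. Five of the six comparisons do not address that hypothesis, and two of them invite within-arm claims.

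If both arms improve equally by 0.3-0.5 SD with r = 0.5-0.7, the misleading pattern occurs in about 17-25% of trials with no treatment effect. The upper end is the mathematical ceiling of 25%, and the figure is much smaller if neither arm changes. The improvement and r are assumptions; only the 20 per arm and the alpha level come from the protocol.

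Any loss of precision is conditional. It is 33% more variance at r = 0.5 and 18% more at r = 0.7 if the effect is read as an interaction with free baseline means. It is 33% and 96% more if it is read as the T1 contrast without baseline. It is nil with a common baseline mean. This should be corrected, but it does not show that the planned analysis is invalid.

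**What to change.** Replace the pairwise sentence with one test per outcome: the Tai Chi minus control difference at T1, adjusted for the same outcome at T0. Use either ANCOVA or the mixed model with unstructured covariance, a common baseline mean and a group effect at T1 only. Report the estimate with a 95% CI. Show within-arm changes descriptively, without p-values, and drop the T0 test and the comparisons that cross arm and time. State that the false discovery rate correction applies to this one contrast across outcomes.

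The cost is analysis wording only. T0 is already measured before randomisation, so no visit, measurement or participant is added.
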